#### Implementation {16c}

One designated staff will generate the allocation sequence by using the randomization program. After research investigators get informed consent from the subject, the staff will assign the patient to the determined group. The operator and other related investigators will be unblinded just before surgery to perform proper management.

### Assignment of interventions: blinding

#### Who will be blinded {17a}

This item is not applicable because the current research is open-labeled.

#### Procedure for unblinding if needed {17b}

This item is not applicable because the current research is open-labeled.

### Data collection and management

#### Plans for assessment and collection of outcomes {18a}

Research investigators are responsible for collecting the baseline, outcome, and other trial data. All data collected will be double-checked by the research staff. All associated assessors will be educated for subjective items: how to measure the ovarian volume by ultrasonography and time to spend to control bleeding, how to estimate the volume of blood loss during operation, and so on.

#### Plans to promote participant retention and complete follow-up {18b}

For all participants, the pelvic examination by ultrasonography will be provided twice (12 weeks and 48 weeks after surgery) for free of charge. If the patient wants to withdraw from this study, she can do it at any time. Investigators must describe the withdrawal reason in the electronic case report form. Investigators may request the patient to use data already collected before the withdrawal. If one agrees to that, incomplete data will be included for the assessment of the results.

#### Data management {19}

As soon as collected, all data will be typed in the electronic case report form by the data manager. Each completed electronic case report form will be double-checked by one or more research investigators. The data without any personal identification information are securely stored in the database. The file of eCRF is locked with a password and accessible to only the designated data manager. The ethics committee of Seoul National University Hospital and Dongguk University Ilsan Hospital will audit study conduct per 12 months.

#### Confidentiality {27}

After data collection, all personal identification information will be deleted, and sequential numbers will be given to data as study subject ID.

#### Plans for collection, laboratory evaluation, and storage of biological specimens for genetic or molecular analysis in this trial/future use {33}

The initial laboratory test, including complete blood count, liver enzyme, BUN, creatinine, and electrolyte will be conducted before operation. After each intervention, only complete blood count will be measured three times: 2 days, 12 weeks, and 48 weeks after the operation. There are no plans to use blood samples in the future.

## Statistical methods

### Statistical methods for primary and secondary outcomes {20a}

Both per-protocol (PP) and intention-to-treat (ITT) populations will be analyzed in two groups. The result will be regarded as valid when the experimental group is not inferior to the control group for the primary outcome, preservation of the ovarian reserve, in both analyzing methods. Serum AMH levels will be analyzed by using the Student *t* or Mann-Whitney *U* tests and repeated measure ANOVA. For secondary endpoints, variables will be analyzed by using the chi-square or Fisher’s exact test for categorical data and the Student *t* or Mann-Whitney *U* test for numerical data. *p* value < 0.05 is considered statistically significant.

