### Trial design {8}

This is an open-label, parallel-group, randomized controlled, non-inferiority trial. Participants with ovarian EMS will be randomly assigned to the experimental (hemostatic agent) and control (suturing) groups at a 1:1 ratio. After surgical treatment of ovarian EMS, we will check the serum AMH and hemoglobin levels and ovarian volumes measured by transvaginal or transrectal ultrasonography before surgery, after 2 days, after 3 months, and after 12 months. Figure 1 shows the schema of this study.

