### Outcomes {12}

#### Primary outcome

The decline ratio of serum AMH levels 12 weeks after surgery: the decline ratio of serum AMH levels is defined as the value of (preoperative AMH levels − postoperative AMH levels)/(preoperative AMH levels). Serum AMH levels will be quantitatively measured by using an enzyme-linked immunosorbent assay.

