### Sample size {14}

The number of participants is determined on the basis of the decline ratio of serum AMH levels 3 months after surgery with a significance level of 2.5% and the test power of 80%. For patients with ovarian EMS treated with laparoscopic suturing, the decline ratio of serum AMH levels 3 months after surgery has been reported to be 24.6% (interquartile range [IQR], 11.6–37.0) in the previous study [14]. From IQR and with the assumption of a normal distribution, standard deviation (SD) was calculated to be 18.81, where SD = IQR/1.349. Although the information on confidence intervals from relevant trials is required for determining the non-inferior margin, there appears no available study for confidence intervals. In one study on the comparison of the preservation of ovarian reserve between hemostatic suturing and electrocoagulation, it was reported that there was no significant difference between the two groups with respect to a reduction rate of serum AMH 3 months after surgery (suturing group 44% ± 28% vs. electrocauterization group 58% ± 24%, *p* = 0.15) [15]. Based on the 14% difference in the rate, we have calculated appropriate numbers of participants for the non-inferior margin from 8 to 14%. The smaller the non-inferior margin, the larger the sample size. Therefore, we set the non-inferior margin at 12% for the primary outcome, which will not be applied for the secondary outcomes because of a lack of relevant references. For the statistical test on non-inferiority with a mean difference of 0, the value for the sample size (*n* = 80) is available with SD of 18.81, and a non-inferior margin of 12% between the two groups, suggesting that the number of participants of each group is estimated to be 40. Supposed that the dropout rate is 10%, the number of participants should be 90 (45 per group).

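### The stated analysis of the primary outcome never uses the 12-point non-inferiority margin on which the trial was sized

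*Protocol article*

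**What the plan says.** - **Design.** Trial design {8}: "This is an open-label, parallel-group, randomized controlled, non-inferiority trial".
- **Primary outcome.** Outcomes {12}: "The decline ratio of serum AMH levels 12 weeks after surgery", defined as the preoperative minus the postoperative level, divided by the preoperative level. A larger value is worse.
- **Sizing.** Sample size {14} works "with a significance level of 2.5% and the test power of 80" (per cent). It takes a true mean difference of 0 and an SD from a cited suturing study ("standard deviation (SD) was calculated to be 18.81, where SD = IQR/1.349"), and it states "we set the non-inferior margin at 12% for the primary outcome". The result is 40 per group, raised to 45 per group (90 in all) for 10% dropout.
- **Analysis.** Statistical methods {20a} requires that the experimental group be not inferior on the primary outcome in both the PP and ITT populations. The methods it names are: "Serum AMH levels will be analyzed by using the Student *t* or Mann-Whitney *U* tests and repeated measure ANOVA". The only threshold in the section is a p "value < 0.05 is considered statistically significant".
- **Agreement of populations.** The section on non-adherence and missing data {20c} adds only that the PP and ITT results must agree.

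Neither {20a} nor {20c} mentions the margin, a confidence limit, a shifted null hypothesis or the 2.5% level.

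**The concern.** A non-inferiority claim needs the data to exclude a disadvantage as large as the margin. A Student t or Mann-Whitney test in its usual form asks whether zero difference can be rejected, and failing to reject zero does not exclude 12 points.

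Two of the named methods also do not estimate the quantity to which the margin applies. The Mann-Whitney test compares ranks and gives no mean difference. A repeated-measures group effect draws on several visits (before surgery, 2 days, 3 months and 12 months), whereas the margin was set for the mean decline ratio at 12 weeks.

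The trial's single primary conclusion is at stake. {20a} requires the agent to be not inferior, but its only numerical criterion is a p-value threshold with no null hypothesis or sidedness. An analyst who followed the section literally would have no instruction for applying the 12 points.

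**Working it through.** **Inputs, all from Sample size {14}:** margin 12 percentage points; SD 18.81; true difference 0; level 2.5%; power 80%; 40 evaluable per group; dropout 10%. The calculations assume normal data, equal SDs and equal groups (1:1 allocation, Trial design {8}).

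**1. Reproduce the plan's sample size.**
- SD from the quoted quartiles: (37.0 − 11.6)/1.349 = 18.83, against 18.81 stated. The gap is immaterial, and 18.81 is used below.
- Normal approximation at one-sided 2.5%: n per arm = 2 × (1.960 + 0.842)² × 18.81² / 12² ≈ 38.6, so 39.
- Exact calculation (noncentral t): 40 per arm, power 80.4%.
- Dropout: 40/0.9 = 44.4, so 45 per arm and 90 in all.
- At one-sided 5% the same inputs need only 31 (normal) or 32 (t) per arm. The stated 40 therefore rests on a one-sided 2.5% test against the margin.

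**2. Precision at 40 per arm.**
- Standard error = 18.81 × √(2/40) = 4.206.
- The 97.5% t quantile on 78 degrees of freedom is 1.991, so the 95% half-width is 1.991 × 4.206 = 8.37 points.

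**3. Compare two rules on the observed difference d (agent minus suturing), if the observed SD is 18.81.**
- Margin rule: d + 8.37 < 12, so d must be below 3.63.
- Non-significant difference test: d must lie between −8.37 and +8.37.
- For d between about 3.6 and 8.4, the difference test is non-significant while the margin rule does not show non-inferiority.

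**4. Chance of passing under each rule (noncentral t, SD 18.81, 40 per arm).**

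| True difference | Two-sided p ≥ 0.05 on a difference test | Upper 95% limit below 12 |
|---|---|---|
| 0 | 95.0% | 80.4% |
| 8 | 53.2% | 15.4% |
| 12 (at the margin) | 19.6% | 2.5% |

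For the last row the noncentrality is 12/4.206 = 2.853. With 45 per arm, the 19.6% becomes 15.1%.

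**5. The two significance levels.** A two-sided 0.05 test puts 2.5% in each tail, so it matches the sizing level. Only if 0.05 were applied one-sided against the margin would the error at a true difference of 12 be 5.0%, twice the level used for sizing.

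**The case against.** Several points on the other side are sound, and they limit the claim.

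- **A reader might infer that the plan's false-positive rate is 19.6%.** The text does not support that. No section says that p > 0.05 means non-inferior. {14} fixes a margin for the primary outcome and {20a} requires the agent to be not inferior in both populations. The 19.6% describes a possible misreading.
- **A reader might infer that 2.5% and 0.05 contradict each other.** They need not, because a two-sided 0.05 corresponds to a one-sided 2.5%. What stands is that sidedness is stated in neither section.
- **A t test can be run against a null shifted by 12 points.** Its confidence interval would then give exactly the rule needed. But {20a} does not say so, and the point does not carry over to the Mann-Whitney test in its usual form or to repeated-measures ANOVA. The ANOVA may be meant only for the longitudinal data; {20a} does not say which method decides.
- **A reader might infer that the wrong variable will be analysed,** because {20a} speaks of AMH levels. This is plausibly shorthand for the decline ratio defined under {12}.
- **A reader might infer that the test will be picked after seeing the data.** The article does not say that, and a rule for choosing between a t and a rank test is detail that an article may leave to a fuller document.

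The appeal to a fuller document does not dispose of the main point. The article does state a primary analysis and a threshold, and these are not connected to the hypothesis on which it sized the trial.

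**Conclusion.** The concern holds in this limited form: the margin in {14} has no stated role in the analysis in {20a}. As usually run, the named tests cannot establish non-inferiority, and two of them do not estimate the 12-week mean difference to which the margin applies. Requiring agreement between PP and ITT does not help if both populations are analysed with a test that ignores the margin.

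The size is conditional. If a non-significant difference were taken as non-inferiority, an agent exactly at the margin would pass in 19.6% of trials instead of 2.5%, given 40 evaluable per arm, SD 18.81 and normal data. The sample size calculation itself reproduces and is not in question. The point should be settled before outcome data are seen, because it governs the only primary conclusion.

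**What to change.** In Statistical methods {20a}, replace the sentence on AMH with one decision rule:

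- Estimate the mean difference, hemostatic agent minus suturing, in the 12-week AMH decline ratio.
- Declare non-inferiority only if the upper limit of the two-sided 95% confidence interval (one-sided 2.5%) is below +12 percentage points in both the ITT and PP populations.
- Label the Mann-Whitney test and the repeated-measures ANOVA as supportive.
- State that p < 0.05 is two-sided and applies to the difference tests on the secondary outcomes. This fits {14}, which already confines the margin to the primary outcome.

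The cost is a few sentences, with no additional patients, visits or measurements. With 40 evaluable per arm the rule has 80.4% power at a true difference of 0, so 80 evaluable and 90 enrolled stand.

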### Interim analyses {21b}

There is no plan of any interim analyses to evaluate the efficacy or worthlessness of this trial. Because both interventions are already widely conducted during laparoscopic ovarian cystectomy, regardless of the current study, there is no reason to terminate the trial even if the results are not statistically significant

### Methods for additional analyses (e.g., subgroup analyses) {20b}

A separate supporting analysis will be conducted for unilateral or bilateral ovarian EMS.

### Methods in analysis to handle protocol non-adherence and any statistical methods to handle missing data {20c}

Both per-protocol (PP) and intention-to-treat (ITT) populations will be analyzed in the two groups. The results will be valid when it is accordant in both analyzing methods.

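### Sections {20a} and {20c} set different conditions for a valid result, and the second is met when ITT and PP agree that non-inferiority failed

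*Protocol article*

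**What the plan says.** In the protocol article, section {20a} (statistical methods for primary and secondary outcomes) states that PP and ITT populations will both be analysed. It then says "The result will be regarded as valid when the experimental group is not inferior to the control group for the primary outcome" and adds that this must hold in both analyses. The next sentence names the tests for AMH: Student t or Mann-Whitney U, and repeated-measures ANOVA. The section closes with a general threshold of p < 0.05.

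Section {20c} (non-adherence and missing data) repeats that both populations will be analysed and says "The results will be valid when it is accordant in both analyzing methods". It names no outcome, direction or margin.

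The margin and error rate appear only in the sample size section {14}: a 2.5% significance level, 80% power, "SD of 18.81, and a non-inferior margin of 12% between the two groups", and a true difference of 0.

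**The concern.** The two sentences use the same word for different conditions. Their answers part when both populations fail to show non-inferiority: the {20c} condition is met and the {20a} condition is not.

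Each sentence also has a weakness of its own. Under {20a}, validity hangs on a favourable outcome, although a failure to show non-inferiority is a proper answer to the question the trial asks. Under {20c}, the only input is whether two heavily overlapping analyses match, whatever they show.

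What is at stake is how a negative trial would be described. The analysis section names difference tests and a p-value threshold, and does not restate the margin or a confidence limit. Two non-significant difference tests agree with each other. Someone applying {20c} alone could call that a valid finding of similarity, although neither analysis excluded a 12-point loss.

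**Working it through.** **Inputs.** From section {14}: SD 18.81 and margin 12 (both in percentage points), true difference 0, significance level 2.5% (sidedness not stated, taken as one-sided), power 80%, dropout 10%, 45 randomised per group. From section {8}: 1:1 allocation. *Assumption:* the article gives no PP loss rate, so PP is taken as a random subset of an ITT set of 45 per arm, with its size varied below.

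**Plan's own figure.** n per arm = 2 × (1.960 + 0.842)² × 18.81² / 12² = 38.6, so 39. With the noncentral t, 39 per arm gives 79.4% power and 40 gives 80.5%, so the plan's 40 per arm is reproduced. Allowing for dropout, 40 / 0.90 = 44.4, so 45 per arm and 90 in total. This supports the one-sided 2.5% reading, which corresponds to a two-sided 95% interval.

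**Agreement against non-inferiority in both.** For a true difference d (agent minus suturing, in decline ratio):

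- SE(ITT) = 18.81 × √(2/45) = 3.97, and SE(PP) = 18.81 × √(2/40) = 4.21.
- P(non-inferior in one set) = Φ((12 − d)/SE − 1.960).
- The two estimates come from nested samples, with correlation √(40/45) = 0.943. The joint probability follows from the bivariate normal.
- P(both fail) = 1 − P(ITT) − P(PP) + P(both succeed). Agreement = P(both succeed) + P(both fail).

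At d = 12 each set succeeds with probability 0.025 and both succeed with probability 0.017. Both fail with probability 1 − 0.025 − 0.025 + 0.017 = 0.967, so agreement is 0.984.

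| True difference (points) | Both non-inferior ({20a} met) | Both fail | Agreement ({20c} met) |
|---|---|---|---|
| 0 | 0.798 | 0.127 | 0.925 |
| 3 | 0.540 | 0.347 | 0.888 |
| 6 | 0.263 | 0.638 | 0.901 |
| 12 | 0.017 | 0.967 | 0.984 |

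Simulation with t-based limits (40,000 trials per value) agrees to within about 0.01.

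**Range over the assumed PP size.** The lowest agreement over all true differences, with 45 per arm in ITT and random loss, is:

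| PP per arm | Minimum agreement |
|---|---|
| 43 | 93.1% |
| 40 | 88.6% |
| 36 | 83.6% |
| 32 | 78.8% |
| 27 | 72.5% |

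**Exclusions that differ by arm.** Section {11b} allows added electrocoagulation, and the Discussion says it may be needed more often with a hemostatic agent. The article does not say whether such patients leave PP. As an illustration only, suppose the excluded experimental patients have a decline 36.3 points larger (50.7 − 14.4, the contrast quoted in the Background), with no true difference among the rest. Agreement falls to about 63% when 5 of 45 per arm are excluded and about 38% when 9 of 45 are.

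**Route to misuse.** In a simulation at a true difference of 6 points (45 and 40 per arm), about 29% of trials had a non-significant two-sided t test in both sets and also failed non-inferiority in both. The analyses agree in these trials, and non-inferiority was not shown.

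**The case against.** The strongest reply is that there is no outright contradiction. Section {20a} says *when*, not *only if*. Non-inferiority in both populations implies that they agree, so the {20a} condition is a special case of the {20c} condition. Section {20c} can be read as a consistency check under the heading on non-adherence, with {20a} as the success criterion. Applying both sentences together gives the {20a} rule, and agreement on failure licenses no non-inferiority claim. Discordant populations fail both conditions, so the sections do not conflict there.

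All of that stands, and it limits the point to wording that needs reconciling. It does not remove the point: the article still gives two conditions for one label, and neither sentence says which governs.

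A reader might go further in three ways that the documents do not support:

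- *That the trial's error rate is inflated.* It is not if {20a} governs.
- *That the two analyses agree about 90% of the time whatever the effect.* That needs a PP loss of about 10% or less, at random. The 10% in section {14} is a dropout allowance, not a PP exclusion rate, and agreement is lower with larger or unequal exclusions.
- *That a negative result would go unreported.* Section {31a} commits to sharing the results without such a condition.

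**Conclusion.** The point holds as an ambiguity to be reconciled. Sections {20a} and {20c} attach *valid* to different conditions, one dependent on a favourable result and the other blind to what the result is. They part whenever both populations fail. With 40 of 45 per arm in PP, that is about 13% of trials at the design's assumed difference of 0 and about 97% at a true difference equal to the margin.

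These figures describe how often the labels differ. They are not rates of wrong decisions, and they rest on normal data, the plan's SD and margin, complete ITT data on 45 per arm and random PP loss. The finding that agreement cannot replace non-inferiority is less sensitive to the PP size: at the margin, agreement stays between 97% and 99% for PP sizes from 27 to 43 per arm, while non-inferiority in both stays at 2% or less.

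**What to change.** Replace the two sentences in {20a} and {20c} with one rule on the difference in 12-week decline ratio (agent minus suturing):

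- Conclude non-inferiority only if the upper limit of the two-sided 95% confidence interval is below 12 percentage points in both ITT and PP.
- Otherwise conclude that non-inferiority was not shown, and report that as the trial's result, including when the two populations disagree.
- Stop using *valid* as a property of the result.

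The rule uses the plan's own margin and significance level and keeps the requirement, already in {20a}, that both populations succeed. It needs no extra patients or data. The downside is that the sponsor commits in advance to reporting a failed non-inferiority result as the trial's answer.

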### Plans to give access to the full protocol, participant-level data, and statistical code {31c}

There are no detailed plans for this item.

## Oversight and monitoring

### Composition of the coordinating center and trial steering committee {5d}

#### Coordinating center

MRCC will act as the coordinating center for this trial.

### Composition of the data monitoring committee, its role, and reporting structure {21a}

[name] (member): a professor at the Department of Obstetrics & Gynecology in Keimyung University School of Medicine, Daegu, Republic of Korea

[name] (member): a professor at the Department of Food and Nutrition in Kookmin University, Seoul, Republic of Korea

[name] (member): a professor at the Institute of Animal Molecular Biotechnology and Department of Biotechnology, College of Life Sciences and Biotechnology

[name] (chairman): a professor at the Department of Obstetrics and Gynecology, Konkuk University Medical Center, Seoul, Republic of Korea

The data monitoring committee (DMC) consists of the four basic and clinical professors. All members are independent of the sponsor and competing interests. Designated investigators send a report, including registration of participants, intervention allocation, reasons for withdrawal, adverse event, and violation of initial protocol, to the DMC members 2 weeks before the DMC meeting. The meetings are scheduled to take place every 6 months but can be held more frequently if concerns arise. Any recommendations of the DMC are immediately passed on to the principal investigator.

